##### Others

24. Patient currently participating in another trial possibly influencing the safety of the patient and/or the outcomes of the study,

25. Pregnancy/Planned pregnancy/Childbearing potential without sufficient measures to prevent pregnancy as judged by the investigator,

26. Known allergy to contrast medium that cannot be adequately controlled with pre-medication,

27. Known intolerance against acetylic-salicylic acid (ASA), heparin, clopidogrel and ticlopidin, cobalt-chromium,

28. Metformin intake not stopped at least 3 days before the intervention.

### Sample Size Calculation, Statistics, and Calculations

#### Sample Size Calculation

The primary endpoint is the difference between treatments in change of eGFR over 12 month. For this endpoint the intention-to-treat population (ITT) will be taken for primary analysis.

Definitions:

• Controls expectation value μ_C_, variance σ_C _^2 ^and group size n_C _= Medication

• Treatment expectation value μ_T_, variance σ_T _^2 ^and group size n_T _= Medication and Stent

A two-sided test will be performed.

• Null hypothesis: H_0_: μ_T _= μ_C_

• Alternative hypothesis: H_A_: μ_T _≅. μ_C _(↔.μ_T _< μ_C _or μ_T _> μ_C_)

• Minimum difference: Δ = μ_T _- μ_C_

• Variances: σ_T _^2 ^and σ_C _^2^

• Level of significance: α

• Statistical power: 1 - β

• Sample size: N = n_T _+ n_C_

##### Calculations

The sample size (N) has been calculated using the methods of Bock J, 1998 [22] and Chow

SC, 2003 [23], N = nT + nC. 4 (u1.α/2 + u1.β)2 (σ/Δ)2 for σC 2 = σT 2 = σ2

The probability for incorrect rejection of H0 for a two-sided test (α/2 = 0.025) is u1-0.025 = 1.9600.

The probability for correct rejection of H0 (1-β = 80%) is u0.8 = 0.8416.

Based on published data [24], the estimated GFR difference between baseline and 12 month follow-up in patients with unilateral RAS>70% is 4.35 ml/min. Moreover, from the DRASTIC study [25] considering the patient population with bilateral stenosis the estimated GFR difference at 12 months was 10.0 ± 16 ml/min. Furthermore, in a usual patient population the proportion of patients with bilateral RAS is 15% to 20%. This leads to a calculated increase of estimated ΔGFR for a mixed cohort of patients with unilateral and/or bilateral RAS of approximately: ΔeGFR = 0.2*10+0.8*4.35 ≈ 5.5 ml/min μ_T _= 5.5 ml/min.

In addition, for the medication group, we can assume an eGFR difference or decrease of

μ_C _= -1.0 ml/min at 12 months follow up.

The relevance level is assumed to be 20% of the difference between the therapy and medication or control group. Therefore, the sample size can be calculated as shown in Table 1.

**Table 1 T1:** Calculation of sample size

**Expectation value**			**Relev**.	**Variance^1/2^**			**Sig. level**	**Statistical**	**Sample**
			
**Therapy**	**Ref**.	**Min. diff**.	**level**	**Therapy**	**Ref**.	**k **=	**1-sided**	**power**	**size**
**mue_T_**	**mue_C_**	**Delta**	**delta**	**sigma_T_**	**sigma_C_**	**n_T_/n_C_**	**alpha = 0.05**	**1-beta**	**N = n_T_+ n_C_**

5.5	-1.0	6.5	2.0	14.0	14.0	1.50	1	0.80	**250**

Considering a drop-out rate of approximately 20%, and a PTRAS rate of 20% of patients being initially randomised to BMT group, a total of 300 patients will be enrolled, 150 patients per group. A study patient that has been withdrawn from the study will not be replaced. It is intended to include between 6 and 24 patients per centre.

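### Table 1's N = 250 at 80% power comes from a one-sided, 1.5:1 calculation with a 2.0 ml/min shift, not from the two-sided, 1:1 ITT test that the protocol plans

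*Protocol article*

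**What the plan says.** Under Sample Size Calculation, the protocol article makes ITT the primary analysis population and states "A two-sided test will be performed". The null hypothesis carries no margin: "Null hypothesis: H_0_: μ_T _= μ_C".

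Under Calculations, the text sets the two quantiles: "The probability for incorrect rejection of H0 for a two-sided test (α/2 = 0.025) is u1-0.025 = 1.9600" and "The probability for correct rejection of H0 (1-β = 80%) is u0.8 = 0.8416". The printed formula has a leading factor of 4, so it assumes equal groups, and it uses only sigma and Delta. The stent arm is expected to gain 5.5 ml/min ("ΔeGFR = 0.2*10+0.8*4.35 ≈ 5.5 ml/min") and the medication arm to change by minus "1.0 ml/min at 12 months follow up", a difference of 6.5. A further sentence adds: "The relevance level is assumed to be 20% of the difference between the therapy and medication or control group".

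Table 1 then lists Delta 6.5, a relevance level of 2.0, SD 14.0 in both arms, k = n_T/n_C = 1.50, a significance column headed 1-sided with alpha = 0.05, power 0.80 and N = 250. The text below the table allows for about 20% drop-out and for a stenting rate of 20% in the medication group, and concludes that "a total of 300 patients will be enrolled, 150 patients per group". The Abstract, Discussion and Conclusion all give 1:1 randomisation.

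**The concern.** The text and the table describe different calculations. The text has a two-sided 5% level, equal groups and no margin. The table has a one-sided 5% level, unequal groups and a subtracted relevance level. Only the table's version leads to the printed N.

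The sample size and its power are therefore not those of the analysis that will be done. A reader cannot recover 250 from the printed formula and cannot tell what power the planned test has. The Discussion and Conclusion rest their expectation of a significant result on this enrolment.

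**Working it through.** **Inputs.** All come from the Calculations section and Table 1: mu_T = 5.5, mu_C = -1.0, Delta = 6.5, sigma = 14 in both arms, power 80% (u = 0.8416). The level is 1.9600 in the text, or 1.6449 for a one-sided 5% level as headed in Table 1. The relevance level is 2.0 in the table, or 20% of Delta in the text.

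**Formula.** For group ratio k and shift delta, by the normal approximation:

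N = ((1 + k)²/k) × (u_α + u_β)² × (sigma/(Delta − delta))²

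With k = 1 and delta = 0 this is the formula printed in the protocol.

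**Reproducing Table 1.** With k = 1.5, one-sided 5% and delta = 2.0:

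(2.5²/1.5) × (1.6449 + 0.8416)² × (14/4.5)² = 249.3, rounded up by group to 100 + 150 = 250.

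The layout of Table 1 is broken in the copy read, so this match is what confirms that the three settings were really used.

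**The printed formula with the text's inputs:**

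4 × (1.9600 + 0.8416)² × (14/6.5)² = 145.6, so 146.

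**Other combinations at 80% power, SD 14 (total N):**

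| Delta − delta | One-sided, k = 1.5 | One-sided, 1:1 | Two-sided, k = 1.5 | Two-sided, 1:1 |
|---|---|---|---|---|
| 4.5 (shift 2.0) | 250 | 240 | 318 | 304 |
| 5.2 (shift 1.3) | 188 | 180 | 238 | 228 |
| 6.5 (no shift) | 120 | 116 | 153 | 146 |

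Only the first cell gives 250. One match exists at 90% power (difference 5.2, one-sided, 1:1), but the protocol states 80% throughout.

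**Relevance level.** 0.20 × 6.5 = 1.3, whereas 2.0/6.5 = 30.8%. With 1.3, Table 1's own method gives 186.7 before rounding, so 188 in whole groups.

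**Where k = 1.50 may come from.** Take 250 patients split 125:125. If 20% of the medication group (25) are stented, 150 patients are stented and 100 are not, a ratio of 1.50. With 150 per arm it is 180:120, again 1.50. The protocol does not state this link, but the match is exact.

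**Power of the planned test (two-sided 5%, 1:1, no margin, SD 14).** 240 is the 300 enrolled less 20%. Under ITT, stenting in the medication group reduces the difference and leaves k unchanged. If crossovers gain the full stent effect, the medication-arm mean becomes 0.8 × (−1.0) + 0.2 × 5.5 = 0.3, and the difference is 5.5 − 0.3 = 5.2.

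| Difference | N for 80% power | Power at 250 | Power at 240 |
|---|---|---|---|
| 6.5 (no dilution) | 146 | 95.6% | 94.9% |
| 5.2 (20% crossover, full effect) | 228 | 83.6% | 82.0% |

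**The case against.** The best defence is that nothing about the trial's conduct or test is in doubt. The hypotheses are two-sided with a null of equality, the Statistical Analyses section plans a t-test or a rank test, and nothing in the document tests against 2.0. The one-sided interval mentioned there concerns proportions (the protocol's relative likelihoods), not this endpoint. The relevance level is thus only a planning input, and it made the sample larger than the printed formula requires. The ratio of 1.50 need not be a different randomisation either, since it matches the 1:1 design after the stated 20% crossover.

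Most of this stands. A reader might infer that the success criterion is ambiguous between a two-sided test against zero and a one-sided test against 2.0. The hypothesis section rules that out. A reader might also infer that patients are to be randomised 1.5:1, but every statement of the allocation says 1:1.

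The defence does not rescue the figures. If k is an as-treated ratio, it does not fit the ITT primary analysis, where groups stay as randomised. The one-sided level and the shift remain at odds with the text, and 2.0 remains at odds with the 20% rule whatever its purpose.

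**Conclusion.** The point holds as a mismatch between the sample size table and the planned test, and it should be fixed. The printed 250 and 80% belong to a one-sided 5% calculation with k = 1.50 and a 2.0 ml/min shift. The stated two-sided, 1:1, no-margin test needs 146 evaluable patients for 80% power on the protocol's own Delta and SD.

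The tempting stronger conclusion is that the trial is underpowered. A 2.0 margin tested two-sided at 1:1 would need 304 evaluable patients and have 71.9% power at 250. No part of the document plans that test. For the test that is planned, power lies between 82.0% and 95.6% over the cases examined (240 or 250 evaluable, with or without dilution), so no shortfall is shown.

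These figures rest on SD 14 and a difference of 6.5, both taken from the protocol, and on the normal approximation. The diluted case also assumes that crossovers gain the full stent effect. That the 20% crossover is the source of k = 1.50 is an inference.

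**What to change.** Replace Table 1 with rows for the planned test: two-sided alpha 0.05, k = 1, no relevance margin, sigma 14. Delete the relevance-level sentence. Treat the 20% stenting rate in the medication group as dilution of Delta under ITT rather than through k.

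Report both cases, so that the undiluted figure does not replace one misleading number with another:

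- Delta 6.5, no dilution: N = 146 for 80% power; power 95.6% at 250 and 94.9% at 240.
- Delta 5.2, with the full-effect crossover assumption stated: N = 228 for 80% power; power 83.6% at 250 and 82.0% at 240.

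The cost is one table and a few sentences. Enrolment, allocation and the primary test stay as they are.

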### Patient population

Three hundred patients will be included to yield at least 250 patients with valid primary endpoint. Patients will be enrolled in approximately 30 centres in Europe and South America. Patient recruitment should be finished within 1 year following the initiation of the last study centre. Study duration would be 4 years.

Selection of participants for this study will be documented on the screening log. The patients being eligible for this study must meet ALL of the following inclusion and NONE of the exclusion criteria.

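### 300 enrolled gives about 240 evaluable at the stated drop-out, not 250, and the stated 20% crossover never enters the effect size; 80% power still holds for the stated two-sided test at SD 14

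*Protocol article*

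**What the plan says.** Under Patient population: "Three hundred patients will be included to yield at least 250 patients with valid primary endpoint".

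Under Sample Size Calculation, the primary analysis is on the intention-to-treat population, the null hypothesis is equality of the two means, and "A two-sided test will be performed". Under Calculations, the normal quantiles are those of a two-sided 5% level and 80% power: "The probability for incorrect rejection of H0 for a two-sided test (α/2 = 0.025) is u1-0.025 = 1.9600" and "The probability for correct rejection of H0 (1-β = 80%) is u0.8 = 0.8416".

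The expected change in the stent arm is derived as "ΔeGFR = 0.2*10+0.8*4.35 ≈ 5.5 ml/min", and that in the medication arm is set at -1.0. Table 1 then lists a difference of 6.5, a relevance level of 2.0, SD 14.0 in both arms, k = 1.50, a one-sided level of 0.05, power 0.80 and N = 250.

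The step to the enrolled number is justified with "Considering a drop-out rate of approximately 20%, and a PTRAS rate of 20% of patients being initially randomised to BMT group", giving 300 patients, 150 per group. Withdrawn patients are not replaced.

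The only spread quoted in the text belongs to the bilateral-stenosis patients of an earlier trial: "the estimated GFR difference at 12 months was 10.0 ± 16 ml/min".

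**The concern.** Two losses are named as the reason for going from 250 to 300. The added 50 patients do not cover the first of them, and the second has no visible effect on any number.

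Crossover matters here because the primary analysis is by intention to treat. A medication patient who receives a stent stays in the medication arm, so any gain from that stent narrows the difference being tested. A 20% narrowing raises the required N by (1/0.8)² = 1.56.

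At stake is whether a reader can tell how many evaluable patients to expect, what intention-to-treat difference the trial is powered for, and whether the stated 80% holds once both losses are counted.

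**Working it through.** **1. Reproducing Table 1.** Formula: N = (1 + k)(1 + 1/k) × [SD × (z_α + z_β)/d]². With d = 6.5 − 2.0 = 4.5, SD 14, one-sided 0.05 (z = 1.645), z_β = 0.8416 and k = 1.5:

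N = 2.5 × 1.667 × (14 × 2.4865/4.5)² = 249.3, or 100 + 150 = 250 in whole patients per arm.

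No other combination tried gives 250:

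| d | Test | Allocation | N |
|---|---|---|---|
| 6.5 | two-sided (the printed formula) | 1:1 | 146 |
| 4.5 | one-sided | 1:1 | 240 |
| 4.5 | two-sided | 1:1 | 304 |
| 5.2 | two-sided | 1:1 | 228 |

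So 250 rests on a one-sided level, unequal allocation and a shift of 2.0. The stated test is two-sided, allocation is 1:1, and the null is equality with no shift. The text also defines the relevance level as 20% of the difference, which is 0.2 × 6.5 = 1.3, not 2.0.

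**2. Drop-out.** 300 × 0.80 = 240. 250/0.80 = 312.5, so 313 to enrol. 250 × 1.2 = 300, which is how the printed figure arises. 300 yields 250 only if drop-out is 1 − 250/300 = 16.7%.

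**3. Crossover.** Let f be the share of the stent effect that crossed-over patients gain by month 12. The protocol does not give f. The difference is then 6.5 × (1 − 0.2f).

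- f = 0: 6.5.
- f = 1: medication mean 0.8 × (−1.0) + 0.2 × 5.5 = +0.3, so the difference is 5.5 − 0.3 = 5.2.

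**4. Power for the stated test** (two-sided 5%, 1:1, equality, 240 evaluable). Power = Φ(d/[SD × √(4/240)] − 1.96). At SD 14 the standard error is 14 × 0.1291 = 1.807.

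- d = 6.5: Φ(3.596 − 1.96) = 94.9%.
- d = 5.2: Φ(2.877 − 1.96) = 82.0%.
- d = 5.2, adding the mixture variance in the medication arm (196 + 0.2 × 0.8 × 6.5² = 202.8 there): 81.4%.
- d = 5.2, SD 16: Φ(2.517 − 1.96) = 71.1%.

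Required N at d = 5.2 and SD 14 is 4 × 7.849 × (14/5.2)² = 227.6, so 228 evaluable and 228/0.8 = 285 enrolled. That is below 300. At d = 5.2 with 240 patients, power reaches 80% only if SD is no more than 5.2/(0.1291 × 2.8016) = 14.4.

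**5. Power on Table 1's basis** (one-sided 5%, shift 2.0, 240 evaluable at 1:1, SD 14).

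- Before crossover, d = 4.5: Φ(2.490 − 1.645) = 80.1%.
- After full dilution, d = 5.2 − 2.0 = 3.2: Φ(1.771 − 1.645) = 55.0%.
- Evaluable N for 80% power at d = 3.2: about 474 at 1:1, or about 494 at k = 1.5.

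**The case against.** The best defence is that nothing important turns on these slips. The drop-out rate is only approximate, the shortfall is 10 patients in 250 (4%), and even on Table 1's one-sided basis 240 patients at 1:1 keep 80.1% power before crossover. For the stated test of equality, 285 enrolled would be enough after both losses. This stands as far as power is concerned. It does not rescue the promise of at least 250, which fails at the stated rate, nor the statement that crossover was taken into account.

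A second defence is that 5.2 is a strong assumption. Study design allows stenting in the medication arm only after severe deterioration or recurrent pulmonary oedema, and at no fixed time. Nothing in the protocol shows that such patients would gain the full effect by month 12. This also stands, so 5.2 should be printed as one end of a range, not as the expected value.

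A reader might infer that the power claim fails outright on the plan's own assumptions. The document does not support that. The stated hypothesis with Table 1's difference and SD, 20% drop-out and full crossover dilution gives 82%.

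A reader might also take 16 as the plan's own SD. It is quoted for a bilateral subgroup of an earlier trial, which carries weight 0.2 in the mixed cohort; the plan's SD is 14. The Discussion says that a pilot study also informed the calculation, and 14 may come from there.

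Finally, one could pair the 2.0 shift with a two-sided level and obtain still lower power, but the protocol nowhere combines the two.

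**Conclusion.** The concern holds in a limited form. The evaluable number is wrong at the plan's own drop-out rate: about 240, not at least 250. The crossover adjustment is claimed but not made.

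Whether this threatens the trial depends on which test is meant. Under the test written in the text, power at SD 14 lies between 82% and 95%, and the 80% claim holds. Under the calculation that generated 250, full dilution brings power to about 55%. The document therefore has to say which basis applies.

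The 82% rests on three assumptions: SD 14, for which Calculations cites no source; normal-approximation power; and full stent effect in every crossed-over patient by month 12. Less effect or later crossover means less dilution. The margin is thin at that end of the range, since an SD above about 14.4 takes power under 80%.

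**What to change.** Keep 300 enrolled and correct the text:

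- Under Patient population, replace the promise of at least 250 with an expected number of about 240 evaluable patients.
- Under Calculations, state the expected intention-to-treat difference as a range from 6.5 (no dilution) to 5.2 (full stent effect in crossed-over patients by month 12), and name the assumption.
- State power for the two-sided 5%, 1:1 test of equality with 240 evaluable at SD 14: about 95% at 6.5 and 82% at 5.2.
- Say that Table 1's 250 comes from a one-sided 0.05 level, k = 1.5 and a shift of 2.0. Reconcile these with the stated test, and the 2.0 with the text's 20% rule. If the shifted one-sided basis is kept, print the fall from about 80% to about 55%.
- Give the source of SD 14, and add SD 16 as a sensitivity figure (about 71% at 5.2), labelled as coming from a bilateral subgroup.

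The cost is restated figures and a corrected table, with no extra patients and no change to conduct, provided the equality test is confirmed as the basis. If the shifted basis is what the sponsor intends, 300 is too few under full dilution: about 474 evaluable at 1:1, or 593 enrolled (474/0.8), would be needed.

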### Secondary endpoints

#### Improvement or stabilisation of renal function

The improvement or stabilisation of the renal function will be determined by change in eGFR at baseline/before start of treatment and 12 months after start of therapy. The following definitions will be used to assess the outcome on the renal function for comparison of the stent plus best medical therapy and the best medical therapy alone group [26]:

• Improvement: Increase of the absolute value of the eGFR after treatment by equal or more than 10% compared to the baseline value

• Stabilisation: Absolute value of the eGFR within ± 10% of the baseline value

• Failure: Decrease of the absolute value of the eGFR after treatment by equal or more than 10% compared to the baseline value.

GFR can be estimated by including serum creatinine with other demographic measurements in a prediction equation. These equations are valid only if the renal function is in a steady state, which can be defined by a constant serum creatinine in a given time interval. The eGFR will be calculated according to the following Modification of Diet in Renal Disease (MDRD) Study Prediction equation: eGFR (ml/min/1.73 m2) = 170 × [serum creatinine, mg/dL]^-0.999 ^× [age in years]^-0.176 ^× [0.762 if female] × [1.180 if black] × [serum urea nitrogen, mg/dL]^-0.17 ^× [serum albumin, g/dL]^+0.318^

#### Renal resistance index

Intra-renal Resistance Index (RI) will be calculated by the following formula: Intra-renal RI = (Peak Systolic Velocity-End Diastolic Velocity)/Peak Systolic Velocity

An intra-renal resistance index difference ΔRI > 0.05 is defined as haemodynamically relevant.

(≥ 70% diameter stenosis) in case of unilateral lesions, with the lower value on the side of stenosis.

#### Restenosis rate

Diagnosis of restenosis will be based on a colour-coded renal duplex sonography. A haemodynamically relevant unilateral restenosis (≥ 70%) is defined by a ΔRI more than 0.05. For bilateral lesions, haemodynamically relevant restenosis is defined by an acceleration time of more than 0.07 sec.

In case of haemodynamically relevant restenosis patients will be treated according to hospital practice.

#### Clinical events

Clinical events will be analysed for:

• Overall combined events (i.e. renal or cardiac death, stroke, myocardial infarction, hospitalisation for congestive heart failure, progressive renal insufficiency (i.e. need for dialysis), need for permanent renal replacement therapy, and need of TVR or TLR),

• renal clinical events (i.e.,. renal death defined as patient death classified according to the *International Classification of Disease*, *Tenth _Revision *(ICD-10) codes N00-N07, N17-

N19, and N25-N27, progressive renal insufficiency (i.e. need for dialysis), need for permanent renal replacement therapy, and need of TVR or TLR),

• MACCE (i.e. cardiac death, stroke, myocardial infarction, hospitalisation for congestive heart failure),

• individual events.

#### Determination of technical success

Technical success defined as successful access and deployment of the device with appropriate lesion coverage, stent positioning and patency determined by angiography at the time of deployment [27].

#### Procedural success

Acute procedural success defined as residual percent diameter stenosis <30% by quantitative computerised angiography [27]. Percent diameter stenosis is calculated as residual target lesion lumen divided by diameter reference segment. Procedural success defined as successful lesion crossing and stent positioning without the occurrence of a serious adverse events up to the moment the introducer sheath is removed [27].

#### Evaluation of blood pressure

Blood pressure will be monitored in every patient throughout the study as part of the basic medical care. In addition to that 24 hour ambulatory blood pressure will be recorded at randomisation, post procedure, at 2, 6 and 12 months (except post procedure for conservative group).

After completion of the study, average 24 h-blood pressure will be analysed and categorised according to the following definitions [34]:

• Cure: Diastolic blood pressure < 80 mm Hg and systolic blood pressure < 125 mmHg, off anti-hypertensive medications.

• Improvement: Diastolic blood pressure < 80 mmHg and/or systolic blood pressure < 125 mmHg on the same or reduced number of medications, or a reduction in diastolic blood pressure by at least 15 mmHg on the same or reduced number of medications.

• Failure: no change or inability to meet above criteria for cure or improvement.

• Benefit: cure or improvement.

#### Left ventricular mass index

Left ventricular mass index (LVMI) will be assessed by echocardiography or MR angiography at baseline and 12 months. LVMI (g/m^2^) is defined as the left ventricular mass divided by the body surface [m^2^]. Parameters for assessing myocardial muscle mass will be acquired by an experienced examiner according to the Guidelines of the American Society of Echocardiography. Therefore, myocardial muscle mass is calculated by using the method described by Devereux and Reichek, or as supplied by the manufacturer of the ECHO device. It has to be ensured that the same method is used in an individual patient.

